### Monitoring, Quality Control, and Data Management

An auditor, independent of the departments involved in the trial, including those responsible for monitoring, will inspect the medical institution and other facilities to ensure the trial is conducted appropriately.

### Ethical Approval

This trial will be conducted in compliance with the Declaration of Helsinki, the Pharmaceutical and Medical Device Act, the Ministerial Ordinance on Good Clinical Practice for Medical Devices, and all other relevant guidelines (jRCT1030230650). The study was approved by the Institutional Review Board of the University of Tokyo School of Medicine (approval number 2023336NI). We will obtain written informed consent from all study participants, and all patient data will be pseudonymized. Patients will receive compensation of JPY 30,000 (approximately US $200) at the end of E4.

The participant information materials and informed consent form are available from the corresponding author (KW) upon request. Any amendments to the protocol will be submitted for review and approval by the institutional review board. Study findings will be disseminated through peer-reviewed publications and conference presentations.

### Outcome Measures

#### Primary Outcome

The primary outcome of this study is the between-group difference in the change in HbA_1c_ from baseline (E0) to either the end of the intervention period at week 12 (E3) or, for patients who discontinue before E3, the point of discontinuation. A reduction of 0.3 percentage points in HbA_1c_ is considered clinically significant [75,76].

#### Secondary Outcomes

Secondary outcomes (Table 5) include health measures, bedtime and sleep measurements, other behavior change assessments, and evaluations of actigraph and diary usage. We will also assess safety outcomes, including hypertension requiring medical assistance (evaluated from system records), subjective hypoglycemia, lower back pain, and pain in the lower extremities (tarsus, thighs, knees, calves, shins, ankles, and feet), as well as any other adverse events (all assessed through patient interviews).

**Table 5 table5:** Secondary outcomes investigated in the study.

Measurements	Outcomes
Differences in changes	Hemoglobin A_1c_ (%) (only after the end of the observation period)^a^ Weight (kg)^a^ BMI (kg/m^2^)^a^ Systolic blood pressure/diastolic blood pressure (mmHg)^a^ Estimated glomerular filtration rate (mL/min/1.73 m2)^a^ Fasting blood sugar (mg/dL)^a^ Low-density lipoprotein cholesterol (mg/dL)^a^ High-density lipoprotein cholesterol (mg/dL)^a^ Neutral fat (mg/dL)^a^ Urine albumin-to-creatinine ratio (mg/gCr)^a^ PSQI-J^a,^^b^
Differences in the measured values	Survey on past bedtimes^a^
Difference in proportions	Behavior change questionnaire^a^
Observed data	Elements of the bedtime questionnaire: attitude, subjective norms, perceived behavioral control, intention^c^ Sleep time calculated from iAide2’s sleep data and diary data^d^ Time in bed calculated from bedtime and wake-up time recorded in the diary for each period^d^ Bedtime recorded in the diary for each period and bedtime sent from iAide^d^ Steps recorded by iAide2^d^ Achievement rate of target bedtime^e^ Number of barriers and coping strategies set and implemented in the diary for the intervention period^e^ Percentage of use of each drug^f^ Percentage of new additions for each drug since consent was obtained^g^ Changes in antidiabetic drugs since consent was obtained (strengthened, unchanged, or attenuated)^g^

^a^Evaluate the differences after the end of the intervention period (at 12 weeks) and after the end of the observation period (at 24 weeks) from the time of consent acquisition.

^b^PSQI-J: Pittsburgh Sleep Quality Index, Japanese version.

^c^Evaluate the differences in the measured values for the following items at 10 weeks and after the end of the observation period (24 weeks).

^d^Evaluate the differences in the average change from the trial period in the 2 weeks before the end of the intervention period.

^e^Evaluate the rates weekly during the intervention period, for the intervention group.

^f^Evaluate the differences in percentages at the time of consent acquisition, at the time of actual registration, after the end of the intervention period, and after the end of the observation period.

^g^Evaluate the difference in proportions after the intervention period and after the observation period.

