**Surveys and questionnaires**					
	Screening at E0	Yes		Yes	
	Sleep and Transtheoretical Model Questionnaire at E0, E3, and E4	Yes		Yes	
	Feedback survey	Yes		No	
	TPB questionnaires at E1	Yes		No	
	Ask if taking any medication that may affect one’s sleep at E0, E1, E3, and E4	Yes		Yes	
	Obtain information about medications, including type 2 diabetes treatments and other drugs, either by asking the patients or by checking their medical records at E0, E1, E3, and E4	Yes		Yes	
	Measure height at E0, and measure weight and blood pressure at E0, E1, E3, and E4	Yes		Yes	
	Ask about any adverse events or malfunction in iAide2 at E1, E3, and E4	Yes		Yes	
	TPB questionnaires at E3 and E4	Yes		Yes	

^a^TPB: Theory of Planned Behavior.

For the intervention group, daily and weekly messaging will deliver a TPB-based intervention targeting PBC and ABC (Figure 2). A researcher or clinical research coordinator (CRC), under the supervision of the researcher, will establish a baseline bedtime and set an initial goal for an earlier bedtime. They will also assist patients in identifying barriers to an earlier bedtime and developing coping strategies. Intervention group patients will receive a daily SMS text message assessment of their performance relative to their target bedtime and will record whether they implemented their coping strategies each day. They will also receive weekly assessments of their progress toward the goal, along with an updated target bedtime, via weekly SMS text messages. Additionally, they will determine coping strategies for the upcoming week.

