We will use a Transtheoretical Model (TTM) questionnaire to categorize participants into the contemplation stage (willing to change health behavior within the next 6 months), preparation stage (willing to change health behavior within the next month), or action stage (has already made modifications to health behavior) [63]. In our previous study, patients in the contemplation and preparation stages were more likely to prefer smartphone-based self-management tools than those in the precontemplation stage [64]. Therefore, we will target patients in the contemplation, preparation, or action stage of increasing their sleep duration by 1 hour per day.

Screening surveys.STOP-J (Snoring, Tiredness, Observed Apnea, High Blood Pressure Screen, Japanese version): screening for obstructive sleep apnea [65]ISI-J (Insomnia Severity Index, Japanese version): screening for insomnia [66]IRLSQ-J version 2.2 (International Restless Legs Syndrome Study Group Rating Scale, Japanese version): screening for restless legs syndrome [67]AUDIT-C-J (Alcohol Use Disorders Identification Test—Consumption, Japanese version): screening for alcohol use disorder [68,69]PHQ-8-J (Patient Health Questionnaire-8, Japanese version): screening for major depression [70,71]TTM (Transtheoretical Model) Sleep Questionnaire: assess the TTM stage [63] relative to sleeping 7 or more hours nightly

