We will provisionally register patients who meet the eligibility criteria at E0. At this stage, each participant will receive an actigraph (iAide2) and will be instructed to wear it 24 hours a day, except when bathing, to press the Event button at bedtime, and to record their bedtimes and risetimes in the diary. Patients who fail to press the Event button for 7 or more days or fail to complete the diary for 7 or more days during the run-in period will be excluded to ensure adequate participation. Data collected during the run-in period will be used to confirm eligibility and establish baseline sleep and step counts. We will randomize eligible participants in a 1:1 ratio to either the intervention or control group using covariate-adaptive randomization by minimization to ensure balance across age (<65 and ≥65 years), sex, HbA_1c_ (<8.5% and ≥8.5%), and institution [72]. Random allocation will be conducted via the Internet Data and Information Center for Medical Research cloud, provided by the University Hospital Medical Information Network, an internet-based central randomization system. A research co-investigator will access the University Hospital Medical Information Network Internet Data and Information Center for Medical Research cloud and input the required baseline information. The system will then securely generate the allocation result immediately before assigning each participant to a group. This process ensures that researchers cannot access or predict allocation results in advance, minimizing potential bias.

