In the secondary analysis, changes in HbA_1c_ at week 12 (E3) and week 24 (E4) will be analyzed using the same approach as in the primary analysis. The proportion of patients with HbA_1c_ below 7% at E3 and E4 (or at the point of discontinuation, if earlier) will be compared between groups using the Fisher exact test. Changes from baseline in step counts, various laboratory test values, and questionnaire scores at E3 and E4 (or at the point of discontinuation, if earlier) will also be analyzed as key endpoints. Changes in T2D medications, categorized as weakened, unchanged, or strengthened, will be compared between groups using the Cochran-Mantel-Haenszel test. The proportion of newly added medications will be compared between groups using the Fisher exact test. A paired (2-sample) *t* test will be used for within-group comparisons of changes in TPB Questionnaire measurements over weeks 0 (E1), 10 (E2), 12 (E3), and 24 (E4). Changes in TPB Questionnaire and SRB Questionnaire measurements between week 12 (E3) and week 24 (E4) will be compared using a *t* test. A paired *t* test will also be used for within-group comparisons from week 0 (E1) to week 12 (E3) for goal achievement rate, goal increment rate, goal reduction rate, average number of coping strategies implemented per day, and the number of identified barriers.

As an exploratory analysis, we will use linear regression to examine the relationship between the average number of coping strategies implemented per day and improvement in HbA_1c_ within the intervention group. The model will include the average number of coping strategies implemented per day and baseline HbA_1c_ as explanatory variables, with the change in HbA_1c_ as the response variable. Changes from baseline to week 12 (E3) and week 24 (E4) (or the point of discontinuation, if earlier) will be assessed.

We will perform a statistical analysis of safety outcomes by calculating the frequency, number of cases, and percentage of individuals experiencing adverse events during the trial, intervention, and observation periods. For the intervention and observation periods, data will be compiled separately for each group, and the percentages will be compared between groups using the Fisher exact test.

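### The stage-of-change outcome is set as a difference in proportions, without saying which proportion or clearly using stage order or entry stage; read that way, the comparison loses power

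*Protocol article*

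**What the plan says.** Table 5 (Secondary Outcomes) sorts outcomes by type of measure. The "Behavior change questionnaire" is the only entry in the row "Difference in proportions". That row is separate from the rows for differences in changes and differences in measured values.

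The table does not call the instrument TTM. The other questionnaires are placed elsewhere: the PSQI-J under differences in changes, the survey of past bedtimes under measured values, and the Theory of Planned Behavior items under observed data. Table 1 lists a "Sleep and Transtheoretical Model Questionnaire at E0, E3, and E4" for both groups, so TTM stage is the natural reading.

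Four other statements bear on the point:

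- Patient Recruitment uses the TTM to "categorize participants into the contemplation stage (willing to change health behavior within the next 6 months), preparation stage" or action stage, which is an ordered scale. Patients in any of these three stages may enter.
- Allocation is made "using covariate-adaptive randomization by minimization to ensure balance across age", sex, HbA1c and institution. TTM stage is not a factor.
- Footnote a of Table 5, attached to this outcome, evaluates differences at 12 weeks and "after the end of the observation period (at 24 weeks) from the time of consent acquisition".
- Statistical Analysis covers "Changes from baseline in step counts, various laboratory test values, and questionnaire scores at E3 and E4". For diabetes-drug change, the other ordered three-level outcome, it says that changes "categorized as weakened, unchanged, or strengthened, will be compared between groups using the Cochran-Mantel-Haenszel test". It names no test for TTM stage.

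**The concern.** A proportion keeps one cut of an ordered scale and discards every move that does not cross it. If the cut were at action or above, a move from contemplation to preparation would count for nothing. A patient who entered in action and stayed there would count as a success in either arm.

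Entry stage is known for every patient and is likely to be a strong predictor of later stage. A comparison that does not use it is less precise than it need be. This is the trial's only stage-of-change measure, and the Discussion stresses the intermediate behavioural steps. What is at stake is a real shift in stage that the comparison could easily miss at 35 patients per arm.

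**Working it through.** **The plan's own figure.** The protocol states no size or power for this outcome. Its only sample size is for HbA1c: a difference of 0.3, SD 0.41, two-sided 5%, 80% power. The normal formula gives 2 × (1.960 + 0.842)² × 0.41² / 0.3² = 29.3, so 30 per arm. The t-based solution is 30.3, so 31, as stated. Then 31 / 0.9 = 34.4, so 35 per arm and 70 in total. This reproduces, and 35 per arm is used below.

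**Assumed inputs (none is in the document).** Entry mix contemplation/preparation/action is 40/35/25%. Control-arm stage at E3 has four levels:

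| Entry stage | Precontemplation | Contemplation | Preparation | Action or above |
|---|---|---|---|---|
| Contemplation | 15% | 55% | 20% | 10% |
| Preparation | 5% | 25% | 45% | 25% |
| Action | 2% | 13% | 20% | 65% |

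The intervention multiplies the odds of a higher stage by a common odds ratio (OR).

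**Step 1: one proportion, by formula.** The cut at action or above is an illustration, not the plan's.

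- Control: 0.40 × 0.10 + 0.35 × 0.25 + 0.25 × 0.65 = 0.290.
- Intervention, OR 3: the entry-stage proportions become 0.250, 0.500 and 0.848, so 0.100 + 0.175 + 0.212 = 0.487.
- SE under no effect: √(2 × 0.388 × 0.612 / 35) = 0.1165. SE under the effect: √((0.290 × 0.710 + 0.487 × 0.513) / 35) = 0.1141.
- Power = Φ((0.197 − 1.96 × 0.1165) / 0.1141) = Φ(−0.275) = 39%.

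Simulation gives 40%, which agrees.

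**Step 2: add entry stage, then order (simulation, 6,000 trials per row).**

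| OR | Proportion, unadjusted | Proportion, stratified by E0 stage | Rank test, unadjusted | Rank test, stratified by E0 stage |
|---|---|---|---|---|
| 3 | 40% | 48% | 51% | 62% |
| 4 | 57% | 68% | 69% | 80% |

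The full gap is 62 − 40 = 22 points at OR 3 and 80 − 57 = 23 points at OR 4.

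**Step 3: other assumptions.** Here OR is 3.3, the entry mix is 40/35/25% or 30/30/40%, and the dependence of E3 stage on entry stage is 1.0 to 1.5 log odds per stage.

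- Fisher test on action or above: 33–46%.
- Change in that proportion since E0: 41–47%.
- Ordered stage stratified by E0 stage: 67–74%.

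Taking midpoints, the gap is 70.5 − 39.5 = 31 points against Fisher and 70.5 − 44 = 26.5 points against the change in proportion. Part of the gap against Fisher is that test's conservatism (type I error about 3%).

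**Step 4: an effect that is not a common odds ratio.** Suppose the intervention only moves 30–40% of those below action straight into it. Stratifying the proportion by E0 stage then raises power from 21–53% to 36–67%. The gain from entry stage therefore does not depend on proportional odds.

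**Step 5: chance imbalance at entry, with no effect.**

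- SE of the between-arm difference in the share entering in action: √(2 × 0.25 × 0.75 / 35) = 10.4 points, and √(2 × 0.40 × 0.60 / 35) = 11.7 points.
- Overall type I error of the unadjusted proportion test: 4.7–5.0%.
- An imbalance of 5 or more action-stage patients occurs in about 21% of trials. Within those, type I error is about 9% unadjusted and about 5% stratified.
- Expected shift from an imbalance of exactly 5: patients entering below action reach it at (0.40 × 0.10 + 0.35 × 0.25) / 0.75 = 0.17, so (5/35) × (0.65 − 0.17) = 6.9 points.

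**The case against.** The strongest reply is that a row label is not a test. Footnote g of Table 5 also speaks of proportions for diabetes-drug change, yet Statistical Analysis assigns that outcome a Cochran-Mantel-Haenszel test. The label therefore does not rule out an ordered test for stage, and the test may sit in a statistical analysis plan that is not shown. This stands. It limits the point to a conditional one: what is lost if the label is taken at its word. The clarification is given for drug change only, and for stage the label is all the article offers.

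A reader might go further in three ways that the document does not support:

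- **That the plan ignores entry stage.** Footnote a refers the comparison to consent, and Statistical Analysis speaks of changes from baseline in questionnaire scores. Either may mean a change since E0. Neither says whether that is patient by patient, and the scores sentence may concern the PSQI-J rather than stage.
- **That entry-stage imbalance will produce false positives.** Randomisation keeps the overall error near 5%. The excess exists only in trials where a sizeable imbalance has occurred, as with any unstratified baseline variable.
- **That the plan prescribes a Fisher test on action or above.** It states no cut and no test for this outcome.

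It is also fair that bedtime, time in bed, sleep time and the Theory of Planned Behavior items carry most of the evidence on intermediate steps, and that TTM stage serves chiefly as an entry filter.

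**Conclusion.** The concern holds in a limited form. The article fixes a summary measure for an ordered outcome without saying which proportion, and its use of stage order and entry stage is unclear. Taken at its word, a single proportion or a change in it would cost roughly 20 to 35 points of power against an ordered comparison stratified by E0 stage. That range assumes 35 per arm, a common odds ratio of about 3 to 4, and stage distributions that the document does not supply; other distributions would give other figures. The validity of the test is not in question: overall type I error is unaffected, and imbalance matters only conditionally. The weight is minor: one secondary outcome in a 70-patient pilot powered on HbA1c.

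**What to change.** Keep the stage proportions at E3 and E4 as description. Compare ordered TTM stage between groups at E3 and at E4, stratified by or adjusted for E0 stage. A stratified Cochran-Mantel-Haenszel mean-score test, a van Elteren test, or a proportional-odds model with E0 stage as covariate would each serve. If a binary result is kept, state the cut and stratify by E0 stage. Name the instrument in Table 5, and say whether the sentence on questionnaire scores applies to it.

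The cost is a line or two of wording, since stage is already recorded in both arms at all three visits. The downside is a less familiar effect measure, which the descriptive proportions offset. The article reports that analysis is under way. The rule should be fixed before this outcome is compared by arm; if that has already happened, the ordered analysis should be labelled post hoc.

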## Methods

### Study Overview

This single-blinded, multicenter pilot study is a 2-arm randomized controlled trial designed to evaluate the efficacy of the BedTime mHealth intervention in promoting earlier bedtime behavior and increasing sleep duration among short-sleeping patients with T2D. The trial will be conducted and reported in accordance with CONSORT (Consolidated Standards of Reporting Trails) guidelines. As outlined in Figure 1, the study begins with recruitment (E0), followed by a baseline measurement period (nominally 2 weeks, but at least 7 days), and then randomized assignment to intervention and control groups (E1). Patients in the intervention group will record their daily bedtime, sleep duration, and step count using an actigraphy device, with TIB assessed via sleep diaries. They will receive weekly bedtime goals, daily feedback on their bedtime performance relative to these goals, and guidance to identify personal barriers to an earlier bedtime along with strategies to overcome them. The control group will also record daily bedtime, sleep duration, and step count using an actigraphy device, with TIB assessed via sleep diaries, but they will receive no feedback and will not be assigned goals. During week 10 of the intervention period (E2), the intervention group will complete a TPB questionnaire. The intervention will last for 12 weeks, followed by end-of-intervention assessments of the primary and secondary outcomes (E3). After the intervention period, there will be an observation phase, nominally 12 weeks in length, but its duration will depend on the date of the final visit (E4), which may occur between 10 and 14 weeks after the intervention ends. The study will be conducted over 1 year, from February 8, 2024, to January 22, 2025.

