**Diary**					
	Enter bedtime and risetime	Yes		Yes	
	Define barriers and coping strategies and report the number of coping strategies implemented	Yes		No	
	TPB^a^ questionnaire at E2	Yes		No	

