E1	Registration, allocation, and beginning of the intervention	Beginning of the intervention	Verify that run-in diary and iAide recording do not cause exclusion Finalize registration and allocation Collect medication status Intervention only: conduct surveys (TPB^i^ Questionnaire, SRB^j^ Questionnaire) Distribute the intervention diary or the control group diary Check for malfunctions or adverse events during run-in
Intervention period	Ongoing measurement	From E1 for 12 weeks	Patients record daily bedtime and risetime, with automated (blinded) measurements of sleep parameters and step count Intervention only: daily feedback, weekly self-set barriers and coping strategies via diary, weekly personalized target bedtime setting via SMS text messages
E2	Ongoing measurement	End of 10 weeks from E1	Intervention only: conduct TPB Questionnaire via diary
E3	End of the intervention	End of 12 weeks from E1	Collect physical data: hemoglobin levels, albumin, uric acid, blood urea nitrogen, estimated glomerular filtration rate, creatinine, fasting blood glucose, HbA_1c_, low-density lipoprotein cholesterol, high-density lipoprotein cholesterol, triglycerides, urine specific gravity, urinary protein, urine albumin-to-creatinine ratio, body weight, and blood pressure measurements Collect medication status Conduct surveys (TTM Sleep Questionnaire, TPB Questionnaire, SRB Questionnaire, PSQI-J) Intervention group: conduct survey (feedback survey) Collect actigraph (iAide2) and intervention period diary Check for malfunctions or adverse events
E4	End of follow-up	End of 24 weeks from E1	Collect physical data: hemoglobin levels, albumin, uric acid, blood urea nitrogen, estimated glomerular filtration rate, creatinine, fasting blood glucose, HbA_1c_, low-density lipoprotein cholesterol, high-density lipoprotein cholesterol, triglycerides, urine specific gravity, urinary protein, urine albumin-to-creatinine ratio, body weight, and blood pressure measurements Collect medication status Conduct surveys (TTM Sleep Questionnaire, TPB Questionnaire, SRB Questionnaire, PSQI-J)

^a^HbA_1c_: hemoglobin A_1c_.

^b^STOP-J: Snoring, Tiredness, Observed Apnea, High Blood Pressure Screen, Japanese version.

^c^ISI-J: Insomnia Severity Index, Japanese version.

^d^IRLSQ-J version 2.2: International Restless Legs Syndrome Study Group Rating Scale, Japanese version.

^e^AUDIT-C-J: Alcohol Use Disorders Identification Test—Consumption, Japanese version.

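### The TPB constructs are to be evaluated at week 10, when only the intervention group is measured, while the end-of-intervention comparison at E3, measured in both groups, is not named

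*Protocol article*

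**What the plan says.** **Outcome definition.** Table 5 (Secondary Outcomes) lists "Elements of the bedtime questionnaire: attitude, subjective norms, perceived behavioral control, intention^c" and so ties the four constructs to footnote c: "Evaluate the differences in the measured values for the following items at 10 weeks and after the end of the observation period (24 weeks"). Week 12 (E3) is not in that footnote.

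**Measurement schedule.** Three places give the week-10 questionnaire to one group:
- Study Overview: "During week 10 of the intervention period (E2), the intervention group will complete a TPB questionnaire".
- Table 1, Diary block: the row "TPB^a^ questionnaire at E2" reads Yes for intervention and No for control.
- Table 4, row E2: "Intervention only: conduct TPB Questionnaire via diary".

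The E1 questionnaire is also intervention-only (Table 1; Table 4, row E1). By contrast, the Table 1 row "TPB questionnaires at E3 and E4" reads Yes for both groups.

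**Analysis.** The Statistical Analysis section names two TPB analyses. One is a paired t test "for within-group comparisons of changes in TPB Questionnaire measurements over weeks 0 (E1), 10 (E2), 12 (E3), and 24 (E4"). The other reads "Changes in TPB Questionnaire and SRB Questionnaire measurements between week 12 (E3) and week 24 (E4) will be compared using a" t test. A general sentence adds that changes from baseline in questionnaire scores will be analysed at E3 and E4, without naming TPB.

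**The concern.** The outcome definition and the schedule do not fit together. If footnote c means a difference between groups, as its wording and the week-24 visit suggest, its week-10 half has no control data. The visit at which a randomised comparison would show the effect of BedTime at the end of treatment is absent from the footnote, and the analysis section does not supply it.

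This matters because the intervention is built to raise perceived behavioral control, and the Discussion says that an HbA1c improvement alone is not enough and that the study is meant to yield evidence on the intermediate steps. As written, the evidence on TPB at the end of the intervention would be before-after change in the intervention group alone. That is open to repeat-testing and time effects. The authors themselves expect that recording bedtimes may change behavior in controls, so a within-group change cannot be credited to BedTime.

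**Working it through.** **1. Who has TPB data at each visit** (planned allocation 35 + 35, from Patient Recruitment; visits from Tables 1 and 4):

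| Visit | Intervention | Control | In footnote c? | Between-group difference in values |
|---|---|---|---|---|
| E1 (week 0) | up to 35 | 0 | no | not computable |
| E2 (week 10) | up to 35 | 0 | yes | not computable |
| E3 (week 12) | up to 35 | up to 35 | no | computable, not named |
| E4 (week 24) | up to 35 | up to 35 | yes | computable, appears intended |

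**2. What the named analyses can deliver.**
- Paired within-group tests: controls have no E1 or E2 score, so their only possible pair is E3-E4. Changes from E1 or E2 exist in the intervention group only.
- General change-from-baseline sentence: it cannot give a between-group TPB result, because controls have no TPB baseline.
- E3-to-E4 change: let d3 and d4 be the between-group differences at E3 and E4, and let f be the fraction of d3 kept at E4. If the change is compared between groups, the contrast is d4 − d3 = d3(f − 1). With an assumed d3 of 0.7 SD (illustrative, not in the protocol):
  - f = 1: 0.7 × 0 = 0
  - f = 0.5: 0.7 × (−0.5) = −0.35 SD
  - f = 0: 0.7 × (−1) = −0.7 SD

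  A fully lasting benefit gives zero on this test, so it measures maintenance and not effect.

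**3. The plan's own sample size.** Inputs: difference 0.3, SD 0.41, two-sided 0.05, power 80%. The normal approximation n = 2(1.960 + 0.842)² × (0.41/0.3)² gives 29.3, so 30 per group. The t-based calculation gives 30.3, so 31, as stated. Then 31/0.9 = 34.4, so 35 per group and 70 in total. The figure reproduces, and the point does not depend on it.

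**4. What an unadjusted E3 comparison could detect**, at 80% power and two-sided 0.05. Normal approximation: (1.960 + 0.842) × √(2/n).
- 35 v 35: 0.67 SD (t-based 0.68)
- 31 v 31: 0.71 SD (t-based 0.72)

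**The case against.** Footnote c does not say between groups. Its row in Table 5 is headed as observed data and also holds intervention-only items, and the only test that the Statistical Analysis section assigns to week 10 is within-group. Week 10 may therefore be a loosely worded within-group item. That is possible, but footnote e states the restriction to the intervention group and footnote c does not. Even on the within-group reading, the outcome definition still omits the end of the intervention.

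A reader might go further and infer four things that the document does not support:
- *That no randomised TPB comparison is planned.* Footnote c includes week 24, when both groups are measured, so a valid comparison appears intended there.
- *That the E3-to-E4 change is offered as the efficacy test.* The sentence does not say so, nor does it say whether the comparison is between groups. Maintenance is a legitimate question, since the Discussion gives it as the reason for the observation period.
- *That the Sleep-Related Behavior (SRB) Questionnaire has the same gap.* Table 5 lists a survey on past bedtimes under footnote a, at 12 and 24 weeks. This is probably the SRB, although the article does not state the link.
- *That the E3 comparison is excluded from the trial's plans.* The article is condensed, and the full protocol and SAP are not shown. What can be said is that the article does not name it.

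It also stands that TPB is in neither stated objective, and that bedtime, the target behavior, is measured in both groups.

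**Conclusion.** The point holds as a contradiction between footnote c and the measurement schedule, together with a badly chosen set of time points. A between-group TPB difference at week 10 cannot be computed (up to 35 v 0). The comparison at week 24 can be made but tests persistence. The end-of-intervention comparison at E3 (up to 35 v 35, detectable difference about 0.68 SD, or 0.72 SD with 31 per group) is not named, and neither named TPB analysis replaces it.

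This rests on reading footnote c as between-group, which is inferred, and on the planned 35 per group completing the questionnaire. The effect is limited to a secondary outcome and to what can be claimed about mechanism. The primary HbA1c result is unaffected.

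**What to change.** - Change footnote c to a between-group comparison of TPB construct values at E3 (end of intervention) and E4 (persistence), without a TPB baseline covariate, since controls have none.
- Mark the week-10 values and all changes from E1 as intervention-group only and descriptive.
- In the Statistical Analysis section, describe the E3-to-E4 change as a maintenance analysis and say whether it is within or between groups.

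The cost is a reworded footnote and a sentence or two in the analysis section. The schedule already collects the E3 and E4 questionnaires in both groups, and the sample size does not change. The drawback is timing: the Results section reports that follow-up has ended and analysis is underway, so the E3 comparison should carry a date and be labelled as added late. Its limited sensitivity (about 0.68 SD, unadjusted) should be stated beside it.
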